## Abstract

**Background:**

People with borderline personality disorder (BPD) experience rapid and distressing changes in mood, poor social functioning and have high rates of suicidal behaviour. Several small scale studies suggest that mood stabilizers may produce short-term reductions in symptoms of BPD, but have not been large enough to fully examine clinical and cost-effectiveness.

**Methods/Design:**

A two parallel-arm, placebo controlled randomized trial of usual care plus either lamotrigine or an inert placebo for people aged over 18 who are using mental health services and meet diagnostic criteria for BPD. We will exclude people with comorbid bipolar affective disorder or psychosis, those already taking a mood stabilizer, those who speak insufficient English to complete the baseline assessment and women who are pregnant or contemplating becoming pregnant. Those meeting inclusion criteria and provide written informed consent will be randomized to up to 200mg of lamotrigine per day or an inert placebo (up to 400mg if taking combined oral contraceptives).Participants will be randomized via a remote web-based system using permuted stacked blocks stratified by study centre, severity of personality disorder, and level of bipolarity.

Follow-up assessments will be conducted by masked researchers 12, 24 weeks, and 52 weeks after randomization. The primary outcome is the Zanarini Rating Scale for Borderline Personality Disorder (ZAN-BPD). The secondary outcomes are depressive symptoms, deliberate self-harm, social functioning, health-related quality of life, resource use and costs, side effects of treatment, adverse events and withdrawal of trial medication due to adverse effects.

The main analyses will use intention to treat without imputation of missing data. The economic evaluation will take an NHS/Personal Social Services perspective. A cost-utility analysis will compare differences in total costs and differences in quality of life using QALYs derived from the EQ-5D.

**Discussion:**

The evidence base for the use of pharmacological treatments for people with borderline personality disorder is poor. In this trial we will examine the clinical and cost-effectiveness of lamotrigine to assess what if any impact offering this has on peoples’ mental health, social functioning, and use of other medication and other resources.

**Trial registration:**

Current Controlled Trials ISRCTN90916365 (registered 01/08/2012)

## Background

People with borderline personality disorder (BPD) have disturbances in mood which include affective instability, outbursts of anger, and feelings of emptiness. These are accompanied by negative thoughts about self and poor interpersonal functioning [1]. As many as 2 % of people have BPD [2], and levels are far higher among those in contact with mental health services, particularly inpatient units, where up to a fifth of people may have this diagnosis [3]. People with BPD have poor social functioning, are socially isolated, and are usually unemployed or on long-term sick leave [4]. They also have high rates of deliberate self-harm and a rate of completed suicide that is 50 times that in the general population [5].

No drugs are currently licensed for BPD; however, people with this condition are usually prescribed large amounts of psychotropic medication [6]. The prominence of affective instability among people with BPD has led to interest in the role that mood stabilizers might play in helping people with this condition. Concerns about toxicity in overdose and harm to children born to women taking these drugs have limited research to date. Evidence from cohorts of people receiving treatment for epilepsy suggests that valproate and lamotrigine may be safer in overdose than carbamazepine [7] and that congenital malformations are more common among people taking valproate than among those taking lamotrigine [8].

To date, there have been two small-scale randomized trials of lamotrigine. The first involved 24 women recruited mainly from advertisements placed in primary care practices. In comparison with people taking placebo, those taking up to 200 mg of lamotrigine daily were found to have lower levels of anger 8 weeks later [9]. The second trial recruited 28 men and women through websites and television and radio advertisements. Those randomly assigned to receive up to 225 mg of lamotrigine were found to have lower levels of affective instability and impulsiveness 12 weeks later [10]. These studies have a number of limitations, including their focus on short-term outcomes, small sample sizes, and the absence of an economic evaluation. Furthermore, people who took part in them may not have had the degree of severity of the disorder that is seen among people who are generally receiving treatment in secondary care mental health services. Although these studies have demonstrated the feasibility of randomized trials for people with BPD, they have not been sufficiently large to fully test the clinical effectiveness and cost-effectiveness of this approach to trying to help people with this condition.

### Research objectives

The main objectives of the study are to find out whether adding lamotrigine to usual care for people with BPD, compared with those prescribed an inert placebo, improves mental health, social functioning, and quality of life and whether it reduces the incidence of suicidal behaviour and lowers the amount of anti-psychotic and other psychotropic medication that people are prescribed. We will also examine whether adding lamotrigine to usual care for people with BPD, compared with those prescribed an inert placebo, is associated with a higher incidence of side effects and whether adding lamotrigine provides a cost-effective use of resources.

## Methods/Design

The LABILE trial (Lamotrigine And Borderline personality disorder: Investigating Long-term Effectiveness trial) is a multi-centre, two-arm, parallel group, double-blind, placebo-controlled randomized trial with 3-, 6-, and 12-month follow-up assessment. The trial includes an integrated clinical and economic evaluation. A summary of trial design is presented in Fig. 1.

**Fig. 1 Fig1:**
[figure not shown]
Study flow chart

### Study setting

Study participants will be recruited from secondary care mental health services in England, including inpatient units, outpatient clinics, and community mental health teams. There are six recruitment centres in London (Central and North West London NHS Foundation Trust, Oxleas NHS Foundation Trust, and West London Mental Health NHS Trust), the East Midlands (Nottinghamshire Healthcare NHS Foundation Trust and Derbyshire Healthcare NHS Foundation Trust), and the North East of England (Tees, Esk and Wear Valleys Foundation NHS Trust).

### Eligibility criteria

The target population is adults who are at least 18 years old and who meet DSM-IV (Diagnostic and Statistical Manual of Mental Disorders, 4th Edition) diagnostic criteria for BPD [1] and are willing and able to provide written informed consent to take part in the study. Eligibility will be assessed by trained researchers. Exclusion criteria are the following:i).current or past comorbid bipolar affective disorder (type I and II) or psychotic disorder (schizophrenia, schizoaffective disorder, or mood disorder with psychotic features),ii). currently receiving a mood stabilizer (lithium, carbamazepine, or valproate) or have done so within the previous four weeks,iii). known medical history of liver or kidney impairment,iv). cognitive or language difficulties that would preclude people from providing informed consent, andv).any woman who is pregnant or planning a pregnancy or any woman of child-bearing age unless using adequate contraception.

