### Interventions

Those in the active arm of the trial will receive encapsulated generic lamotrigine titrated according to the established British National Formulary protocol (http://www.bnf.org/bnf/index.htm) but with the titration occurring at standardised 14-day intervals. The dose will be altered if participants are also taking the combined oral contraceptive pill, which affects the metabolism of lamotrigine. For those not taking the combined oral contraceptive pill, the starting dose will be 25 mg per day. Depending on the response and tolerance, it will be increased to 50 mg after 2 weeks, 100 mg after 4 weeks, and 200 mg per day after 6 weeks and thereafter. For those who are taking the combined oral contraceptive pill, the starting dose will be 25 mg per day. This will be increased to 50 mg after 2 weeks, 100 mg after 4 weeks, 200 mg after 6 weeks, 300 mg after 8 weeks, and 400 mg per day after 10 weeks.

Trial medication will be issued to patients fortnightly to cover the dose titration period, and subsequent 4-weekly packs will be issued once the maintenance dose is reached. This will ensure that non-adherence and subsequent study withdrawal are dealt with promptly and that large supplies of medication cannot be accumulated by patients who may be at risk of overdosing. Supplies will be issued by the relevant hospital pharmacy services. The lamotrigine and placebo capsules will be kept in a suitable temperature-controlled environment at each site.

Those in the placebo arm of the trial will receive capsules, identical in appearance to those containing active lamotrigine, but backfilled instead with lactose monohydrate. This will be prescribed in the same regime as that used in the active arm of the trial.

Usual care will comprise contact with primary and secondary health services, including access to psychological treatment services and inpatient admission if required. No restrictions will be imposed on the use of other treatments, except that those who remain in the trial will not be prescribed lamotrigine (aside from trial medication) or another anti-epileptic mood stabilizer (lithium, carbamazepine, or sodium valproate). Therefore, our approach will be primarily to record the use of all other medication, document details of dosage, and ensure the follow-up of all randomly assigned participants, irrespectively of the medication they subsequently receive.

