Other strengths are that we are recruiting participants from a broad range of secondary care mental health services and we have limited our exclusion criteria with the aim of generating findings that are generalisable across the NHS in England and in other countries with similar health-care systems. Finally, the study is collecting detailed information about resource use and other costs that will enable us to conduct a high-quality economic evaluation of the impact of adding lamotrigine to usual care of people with BPD.

This trial faces a number of challenges which will need to be overcome if we are to recruit to target. In addition to pressures of workload and other factors that may deter clinicians from referring people to clinical trials, clinicians may be concerned about the impact of the trial on what can sometimes be strained relationships with patients. National guidance on the treatment of people with BPD in England advises against the use of pharmacological treatments and this may deter some clinicians from referring people to the study. Potential participants may be concerned about being asked to take part in a study in which they might be allocated to an inert placebo for a 12-month period. In an attempt to overcome these obstacles, we have developed information for clinicians that emphasises the extent of off-label prescribing of psychotropic medication for people with personality disorder and reminds them that national guidance is based on the relative absence of evidence rather than evidence of lack of effect. Initial discussions with potential participants suggest that many recognise the limitations of current treatment options and that there is considerable interest in taking part in the study.

We have previously concluded that existing evidence is insufficient to recommend the use of lamotrigine or other mood stabilizers in clinical practice [42]. The LABILE study has the potential to reduce this uncertainty by generating high-quality evidence on the impact of adding this drug to the usual care that patients receive over the course of a 12-month period.

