## Trial status

Recruitment is ongoing (218 participants recruited as of end of May 2015).

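### The entry exclusion for mood stabilizers lists three drugs and leaves out lamotrigine, the drug under test

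*Protocol article*

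**What the plan says.** Four places in the protocol article bear on whether a lamotrigine user can enter.

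- **Eligibility criteria, exclusion (ii)** rules out people "currently receiving a mood stabilizer (lithium, carbamazepine, or valproate) or have done so within the previous four weeks". The other four exclusions concern bipolar or psychotic disorder, liver or kidney impairment, capacity or language, and pregnancy or contraception. The same section states: "Eligibility will be assessed by trained researchers".
- **Abstract, Methods/Design** excludes "those already taking a mood stabilizer", with no list of drugs and no look-back period.
- **Interventions** sets the rule for participants after entry, who "will not be prescribed lamotrigine (aside from trial medication) or another anti-epileptic mood stabilizer (lithium, carbamazepine, or sodium valproate".
- **Discussion** says that "existing evidence is insufficient to recommend the use of lamotrigine or other mood stabilizers in clinical practice".

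The question the trial is meant to answer, under Research objectives, is "whether adding lamotrigine to usual care for people with BPD, compared with those prescribed an inert placebo", improves outcomes.

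**The concern.** The entry rule and the on-trial rule use the same three-drug bracket, but only the on-trial rule also names lamotrigine. As written, the entry rule therefore omits the drug being tested.

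This affects who enters and how the result reads for them. A current or recent user who is admitted either goes to placebo, which is a withdrawal, or is restarted at 25 mg per day. For that person the contrast is stopping against restarting. The stated objective concerns adding the drug. The baseline ZAN-BPD score, a covariate in the primary model, might also be measured while the drug, or its recent withdrawal, is still having an effect. Randomization balances such patients between arms in expectation, so this is not a claim of bias between arms.

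**Working it through.** **Is lamotrigine in the excluded class?** The main evidence is a comparison of the text.

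| Place | Drugs named | Governs | Lamotrigine covered? |
|---|---|---|---|
| Abstract | none; general term only | people taking one at entry | yes, if lamotrigine counts as a mood stabilizer |
| Eligibility criteria (ii) | lithium, carbamazepine, valproate | current use and previous four weeks | not named |
| Interventions | lamotrigine, plus the same three | prescribing after entry | yes, by name |
| Discussion | lamotrigine and others of the class | background statement | classed as a mood stabilizer |

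In Interventions, the word *another* places lamotrigine in the class. Naming it separately also shows that the authors did not rely on the three-drug bracket to cover it. Exclusion (ii) has the bracket alone, with nothing to mark it as a set of examples.

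**Which patients does each rule catch?**

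| Patient at screening | Lithium, carbamazepine or valproate | Lamotrigine |
|---|---|---|
| Still taking it | excluded by (ii) | not excluded by (ii) read literally; excluded by the abstract's general wording |
| Stops it in order to enter | excluded by (ii) for four weeks | not excluded by (ii); abstract unclear |
| Stopped within the previous four weeks | excluded by (ii) | not excluded by (ii); not clearly reached by the abstract |
| Would take it alongside trial drug | barred by Interventions | barred by Interventions |

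The gap is in the second and third rows. The Interventions rule closes only the fourth, because it governs prescribing after entry and sets no washout.

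**How long would a restarted patient be below target dose?** From the titration schedule in Interventions:

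- not on the combined pill: 25, 50, 100, then 200 mg per day, reached after 6 weeks;
- on the combined pill: continuing to 300 and then 400 mg per day, reached after 10 weeks.

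Both are shorter than the 12 weeks to the first follow-up, so in the active arm any effect on the 52-week outcome should be slight. The article gives nothing from which to estimate an effect in the placebo arm.

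**Does the sample size depend on this?** The plan's figure was reproduced from the inputs under Sample size (difference 3.0, SD 6.75, two-sided 0.05, 90% power):

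- n per arm = 2 × (1.960 + 1.282)² × (6.75 / 3.0)² = 2 × 10.51 × 5.0625 = 106.4, rounded up to 107; total 214;
- power at 107 per arm = 0.902;
- allowing for 15% loss, 214 / 0.85 = 251.8, rounded up to 252.

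Both published figures are right, and neither depends on exclusion (ii).

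**How many entrants could a correction still govern?** Trial status gives "218 participants recruited as of end of May 2015". Then 252 − 218 = 34 planned entrants remained, and 34 / 252 = 13.5%. This caps the number a correction at that date could reach. It does not measure how many patients are affected.

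**The case against.** The strongest reply is that the operative words in (ii) are the general term, with the drugs as a loose gloss. The Interventions bracket even puts lithium under the anti-epileptics, so these lists are not drafted with much care, and the three drugs may simply have been meant as the mood stabilizers other than the study drug. On that reading, together with the abstract, current users are already out. Co-administration is blocked after entry in any case. The remaining group is recent stoppers, and nothing in the article shows that any such patient exists. The article also condenses a fuller protocol, and the screening form, which is not shown, may name lamotrigine.

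Much of this stands. Exclusion of current users was probably intended, the group left over is narrow, and the article alone cannot show whether the slip is in the trial or only in its published account. It does not remove the inconsistency. A list without any marker of examples can be applied as written by the researchers who screen. The abstract's wording does not clearly reach someone who stopped two weeks ago. No reason is given why a four-week look-back should apply to three mood stabilizers and not to the fourth. Nor is this a detail left to a longer document: the article states a specific list and a specific look-back, and the list is incomplete.

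**Conclusion.** The concern holds as an error in a stated entry rule. Taken literally, exclusion (ii) admits a patient who has stopped lamotrigine to enter or within the previous four weeks, although users of the three listed drugs in the same position are excluded. That does not fit a trial of adding lamotrigine to usual care.

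Its importance is limited. The number of patients cannot be derived from the article and is probably small. No bias between arms is expected, no power or sample size figure moves, and re-titration is complete before the first follow-up. The conclusion assumes that the bracket is applied as a closed list and that no document outside the article already names lamotrigine at entry. If either assumption fails, only the article's wording is at fault. It should be corrected, with medium confidence that it touches the trial itself.

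**What to change.** Insert lamotrigine into the bracket of exclusion (ii), beside lithium, carbamazepine and valproate, and keep the four-week look-back for all four. The entry list then names the same drugs as the on-trial restriction in Interventions and agrees with the abstract.

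Then check the full protocol and the screening form:

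- if either already names lamotrigine, correct the article only;
- if neither does, report how many of those already enrolled had taken lamotrigine in the four weeks before entry, as far as medication records allow.

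The cost is one word, plus a review of medication records in the second case. Few otherwise eligible patients, if any, would be lost, and no analysis or sample size changes.

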### Interventions

Those in the active arm of the trial will receive encapsulated generic lamotrigine titrated according to the established British National Formulary protocol (http://www.bnf.org/bnf/index.htm) but with the titration occurring at standardised 14-day intervals. The dose will be altered if participants are also taking the combined oral contraceptive pill, which affects the metabolism of lamotrigine. For those not taking the combined oral contraceptive pill, the starting dose will be 25 mg per day. Depending on the response and tolerance, it will be increased to 50 mg after 2 weeks, 100 mg after 4 weeks, and 200 mg per day after 6 weeks and thereafter. For those who are taking the combined oral contraceptive pill, the starting dose will be 25 mg per day. This will be increased to 50 mg after 2 weeks, 100 mg after 4 weeks, 200 mg after 6 weeks, 300 mg after 8 weeks, and 400 mg per day after 10 weeks.

Trial medication will be issued to patients fortnightly to cover the dose titration period, and subsequent 4-weekly packs will be issued once the maintenance dose is reached. This will ensure that non-adherence and subsequent study withdrawal are dealt with promptly and that large supplies of medication cannot be accumulated by patients who may be at risk of overdosing. Supplies will be issued by the relevant hospital pharmacy services. The lamotrigine and placebo capsules will be kept in a suitable temperature-controlled environment at each site.

Those in the placebo arm of the trial will receive capsules, identical in appearance to those containing active lamotrigine, but backfilled instead with lactose monohydrate. This will be prescribed in the same regime as that used in the active arm of the trial.

Usual care will comprise contact with primary and secondary health services, including access to psychological treatment services and inpatient admission if required. No restrictions will be imposed on the use of other treatments, except that those who remain in the trial will not be prescribed lamotrigine (aside from trial medication) or another anti-epileptic mood stabilizer (lithium, carbamazepine, or sodium valproate). Therefore, our approach will be primarily to record the use of all other medication, document details of dosage, and ensure the follow-up of all randomly assigned participants, irrespectively of the medication they subsequently receive.

In accordance with the current revision of the Declaration of Helsinki (amended October 2000, with additional footnotes added 2002 and 2004), a participant will have the right to stop trial treatment and to withdraw from the trial at any time and for any reason, without prejudice to his or her future medical care by the physician or at the institution, and is not obliged to give his or her reasons for doing so. The investigator may withdraw a participant from trial treatment at any time in the interests of the participant’s health and well-being or for administrative reasons. A trial participant will be withdrawn from taking the trial medication if he or she experiences a rash that is clinically judged as being associated with lamotrigine. The date and reason for termination of treatment will be recorded. Trial follow-ups will continue after treatment has been withdrawn, unless the participant withdraws consent.

### Assessments

The timing and sequence of all assessments are summarised in Table 1*.*

**Table 1 Tab1:** Study assessment schedule

Assessments	Screening	Baseline	12-week follow-up	24-week follow-up	52-week follow-up
Structured Clinical Interview for DSM-IV Axis II Personality disorders	X	-	-	-	-
Structured Clinical Interview for DSM-IV (SCID-I)^a^	X	-	-	-	-
Hypomanic Checklist	X	-	-	-	-
Alcohol, Smoking and Substance Involvement Screening Test (ASSIST)	X	-	-	-	X
Morisky scale	-	-	X	X	X
Zanarini Rating Scale for Borderline Personality Disorder (ZAN-BPD)	-	X	X	X	X
Beck Depression Inventory	-	X	X	X	X
Acts of Deliberate Self Harm	-	X	X	X	X
Social Functioning Scale	-	X	X	X	X
EuroQoL-5D	-	X	X	X	X
Side Effect Scale	-	X	X	X	X
Modified Adult Service User Schedule	-	X	X	X	X

*DSM-IV* Diagnostic and Statistical Manual of Mental Disorders (4th edition), *EuroQoL-5D* European quality of Life-5 dimensions

^a^Section on bipolar affective disorder (type I and II)

